### Primary feasibility outcomes

Study participants enrolment capacity: The study coordinator will monitor weekly enrollment capacity of each of the study sites using the screening and recruitment log. The average number of participants recruited weekly in the respective study sites will be used to evaluate the minimum required time to reach the sample size. The feasibility of the recruitment in a period of 12 months will be considered in order to capture seasonality.Number of refusals: The number of study participants who refuse to participate in the present pilot will be recorded as well as their reasons using the screening and recruitment log. The sample size was calculated including 10% of non-response. In case of a high rate of refusals (>10%), reasons for refusal will be examined in order to improve the recruitment rate in the trial.Perceptions and acceptability: Semi-structured discussion and interview guides will be piloted prior to the start of the study. All revisions made will be noted and incorporated in the final guide. This will allow easy understanding and the percentage of focus group discussions (FGDs) conducted with the minimum required number of participants will be monitored. All FGDs will be conducted with the objective of 100% of completeness.Study visits completion: The percentage of study participants having completed the study follow-up will be calculated. This will be very helpful for the implementation of the trial. A loss to follow-up < 10% will be considered acceptable.Data quality checks: Missing data will be monitored and quantified in this pilot trial. The objective will be to have less than 1% of missing values.Sample size assumptions: Some variables such as the number of doses of IPTp-SP doses taken during pregnancy, normal birth weight (2500g), peripheral malaria infection, and hemoglobin rate will be monitored in both study groups in order to adjust the final sample size calculation.

### Clinical outcomes

The following procedures will be used to ensure an unbiased assignment of treatment safety and efficacy:The randomization list is generated prior to the beginning of the study.The interpretation of the PCR reading is blinded or masked with regard to the treatment allocation of the patients.An independent data safety and monitoring board (DSMB) will review all safety data.

#### Primary clinical outcome

Prevalence of placental malaria (any category, including past infection)

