## Introduction

Malaria remains a major preventable cause of morbidity, mortality, and adverse birth outcomes in sub-Saharan Africa (sSA). By using a model, Walker and colleagues estimated that without pregnancy-specific interventions in sub-Saharan Africa, 9.5 million pregnant women would have been exposed to infection, leading to 750,000 low birth weight (LBW) deliveries [1]. In areas of stable transmission, parasitemic pregnant women are rarely symptomatic and that severe disease or death from malaria is extremely unusual due to the acquisition of significant levels of anti-malarial immunity [2]. In these regions, the risk of *Plasmodium falciparum* infection increases when women get pregnant, with potential adverse consequences for mothers and their offsprings. Placental sequestration is more common in *P. falciparum* infections [3, 4]. Primigravidae women have the highest risk for malaria infection [5, 6], and malaria infections are associated with maternal anemia and adverse birth outcomes, including fetal loss, intrauterine growth retardation, and preterm delivery [7–11]. Malaria prevalence is highest in the first and second trimester of pregnancy [7] and the risk might not immediately return to pre-pregnancy levels after delivery [12]. To prevent the adverse effects of malaria in pregnancy (MiP), the World Health Organization (WHO) recommends a strategy based on three pillars: insecticide-treated nets (ITNs), effective case management of malarial illness and anemia, and intermittent preventive treatment in pregnancy with sulfadoxine–pyrimethamine (IPTp-SP) [13]. The latter involves the administration of curative doses of antimalarials at predefined intervals (ideally on a monthly basis, with a minimum number of 3 doses) irrespective of malaria infection [14, 15] during the second and third trimesters in malaria-endemic regions. IPTp has been proven to have a great impact on placental malaria (PM), LBW, peripheral malaria infection at delivery, and infant mortality so increasing the number of IPTp-SP doses given is a priority. In Burkina Faso, the National Malaria Control Program (NMCP) has recommended at least 3 doses of IPTp-SP but available information suggests that only 31.5% of eligible women met this recommendation despite observed high levels of antenatal clinic (ANC) attendance [1, 16, 17]. Strategies to increase the number of IPTp-SP doses and the coverage using reminders could improve this health intervention's effectiveness. This present project can be considered as a follow-up of the COSMIC study [18] recommendations whose objective was to determine the protective efficacy of community-scheduled screening and treatment (CSST) using community health workers (CHW) combined with other interventions against PM, the primary clinical outcome. Importantly, adherence to IPTp may be affected by perceptions, acceptability, and contextual factors that need to be understood and therefore improve the effectiveness of health interventions. In addition, the effectiveness of IPTp with sulfadoxine–pyrimethamine is threatened by parasite resistance. There is a progressively diminished efficacy of IPTp-SP in clearing existing infections and a shortening of the post-treatment prophylaxis period [19, 20]. Moreover, pregnant women can generally be infected with low parasites densities between ANCs compromising the outcome of the pregnancy [21]. These sub-infections will be missed in pregnant women due to the performance of current rapid diagnostic tests (RDTs), unable to detect low parasitemia. Nowadays, the new generation of ultrasensitive RDTs (US-RDTs) is being developed with the objective to detect lower density infections but data on their performance are scarce and conflicting in malaria-endemic areas [22–25]. Identifying sub-infections in pregnant women and clearing them with an effective artemisinin-based combination therapy (ACT) such as dihydroartemisinin–piperaquine (DHA-PQ) could improve the pregnancy outcome. DHA-PQ has been proven to be safe and effective, well-tolerated antimalarial with a long post-treatment prophylaxis effect based on the results of studies conducted in Nanoro and elsewhere [26–29]. There is a need to combine strategies in order to tackle the deleterious effects of malaria on both mothers and their offsprings. The main objective of the present study is to assess (1) the recruitment capability of the study sites and (2) feasibility of a study on integrated malaria in pregnancy prevention methods in rural Burkina Faso. The specific objectives are to assess perceptions, acceptability, and behaviors regarding the proposed methods by beneficiaries and service providers, (3) acceptability and behaviors regarding late attendance of ANCs of pregnant women, and (4) health care providers views on factors influencing pregnant women’s uptake of ANC interventions using an acceptability framework developed by Mandeep Sekhon et al.

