#### Inclusion criteria

Gestational age of 16 to 24 weeks at their first bookingAt least (≥) 16 years old (considered as an emancipated minor in Burkina Faso by the ethics committeeResidence in the study area and intention to stay in the area for the duration of the pregnancy and deliveryWilling to deliver at the health facilityWilling to provide biological samples as and when required during the study period (blood and placental biopsy)Ability to provide written informed consent

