#### Intervention group

Prior to each IPTp-SP dose administration, a blood sample will be collected for malaria infection screening using US-RDT and microscopy, Hb measurement, and filter paper confection for parasite genotyping. The date of the next IPTp-SP administration will be planned accordingly and the sequences repeated until delivery. Pregnant women with a positive US-RDT will be treated with a full course of DHA-PQ over 3 days. The first dose will be administered under direct observation during ANC and the subsequent doses of the intervention on days 2 and 3 will be taken unsupervised at home. The treatment observance will be assessed by the field worker at the end of the treatment. In addition, a questionnaire on health and socio-demographic characteristics will be administered as well as a physical examination. A phone call as a reminder will be made 1 week prior to the scheduled date for the second dose of IPTp-SP. If the participant is not reachable, the field worker will visit the household in order to remind the visit date. The objective is to increase the number of IPTp-SP doses per woman.

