#### Control group

In case of signs and symptoms suggestive of malaria infection, the nurse will follow the NMCP recommendations. An HRP-2 RDT will be performed and the participant treated with a full course of AL if positive. The first dose will be administered under direct observation at the ANC clinic, and the subsequent doses on days 2 and 3 will be taken unsupervised at home. Before treatment and regardless of the RDT result, the nurse will systematically collect a blood sample for hemoglobin measurement, microscopy, and filter paper for subsequent genotyping. Blood slides will be read after and treatment will be based on the result of RDTs as recommended by the NMCP in peripheral centers. In addition, a questionnaire on health and socio-demographic characteristics will be administered as well as a physical examination. No reminder will be used for the next ANC visit/IPT-SP dose date.

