#### Control group

After the first IPT-SP dose administration, the date of the second one will be scheduled. No additional screening will be performed in this group. In case of signs and symptoms suggestive of malaria infection, the nurse will follow the NMCP recommendations. An HRP-2 RDT will then be performed and the participant treated with a full course of AL if positive. The first dose will be administered under direct observation during ANC and the subsequent doses on days 2 and 3 will be taken unsupervised at home. Before treatment and regardless of the RDT result during scheduled and unscheduled visits, the nurse will systematically collect a blood sample for hemoglobin measurement, microscopy, and filter paper spot for subsequent genotyping.

Irrespective of the study group, field workers will visit the treated participant on day 3 (final day of treatment) in order to assess uptake and compliance to treatment by administering a short questionnaire to check the empty packaging of the treatment. If the woman is severely ill at the time of the visit (e.g., from malaria or other causes and/or from complications from the pregnancy), they will be referred to the health facility for further care. In order to minimize the non-response in group 2, we will collect a blood sample (microscopy and blood spots) in all pregnant women regardless of the study group at fixed schedule visits: day 60 and day 80.

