### Statistical methods

The randomization will ensure a balanced distribution of baseline characteristics between the two groups. A descriptive methodology will be used to analyze feasibility outcomes. Variables such as completion of the study participants recruitment within 12 months, the percentage of refusals, perception, and acceptability will be summarized per group. The primary clinical outcome will compare the prevalence of placental malaria (defined as the number of positive samples by the total number of samples) in each group and will be examined with logistic regression. This will be adjusted by gravidity, parity, season, and number of DHA-PQ. Appropriate statistical methods will be used to account for the influence of potential confounders (number of SP doses, number of co-morbidities, co-medication, the season of malaria transmission, gravidity, etc).

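### The primary model adjusts for the number of DHA-PQ courses, which belong to the intervention, and names no infection status at enrolment

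*Protocol article*

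**What the plan says.** All references are to the protocol article.

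- **Outcome.** Primary clinical outcome: "Prevalence of placental malaria (any category, including past infection)". No limit is set to infection acquired after randomisation.
- **Entry.** Inclusion criteria: "Gestational age of 16 to 24 weeks at their first" booking. The Introduction states: "Malaria prevalence is highest in the first and second trimester of pregnancy".
- **Primary model.** Statistical methods plans a logistic regression of placental malaria on group: "This will be adjusted by gravidity, parity, season, and number of DHA-PQ". A second, open-ended list of potential confounders follows: "number of SP doses, number of co-morbidities, co-medication, the season of malaria transmission, gravidity, etc". Neither list names infection at enrolment.
- **Who receives DHA-PQ.** Intervention women with a positive US-RDT receive DHA-PQ. Symptomatic controls with a positive standard RDT receive AL.
- **Blood sampling, intervention group.** "Prior to each IPTp-SP dose administration, a blood sample will be collected for malaria infection screening using US-RDT and microscopy", which includes the first dose. Filter paper is taken as well.
- **Blood sampling, control group.** In the section on the initial visit: "Before treatment and regardless of the RDT result, the nurse will systematically collect a blood sample for hemoglobin measurement, microscopy, and filter paper". Under Follow-up: "Before treatment and regardless of the RDT result during scheduled and unscheduled visits, the nurse will systematically collect a blood sample". The Abstract says that infection is assessed at scheduled and unscheduled visits and compared by group.
- **Sample size.** 40% against 25%, 80% power, 5% level, 152 per group; 170 per arm after 10% loss.

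**The concern.** The article compares two packages as wholes, and Intervention description says that components will not be compared separately. The number of DHA-PQ courses is one of those components. A woman's count depends on her assignment and on how often she later tests positive. It is zero for every control who follows the protocol. With that count in the model, the group coefficient contrasts intervention women who received no course, largely those who never screened positive, with all controls. That is not a randomised comparison, and the first of those groups is selected for low risk.

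The count also cannot stand in for baseline infection. It partly records who was positive at enrolment, but in one group only.

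A proper baseline covariate would be useful here. The outcome counts past infection and follow-up starts at 16 to 24 weeks, so some placental events may reflect infection already present or already past at entry. Infection at enrolment is likely to predict the outcome, and the trial appears to collect the blood that would show it. At stake are the interpretability of the primary odds ratio and a small amount of precision.

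**Working it through.** **1. The plan's own figure.** Inputs from Sample size considerations: p1 = 0.40, p2 = 0.25, power 80%, 5% level (taken as two-sided). The pooled proportion is 0.325.

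n = [1.96 × √(2 × 0.325 × 0.675) + 0.8416 × √(0.40 × 0.60 + 0.25 × 0.75)]² / 0.15² = (1.298 + 0.550)² / 0.0225 ≈ 152.

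152 / 0.9 gives 169, against 170 stated. The calculation reproduces, and power at 152 per group is 80.0%.

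**2. What adjusting for DHA-PQ can do.** This is an illustration with assumed inputs. Suppose the intervention has no effect, placental malaria is 40% in both groups, and it is 70% in women infected at enrolment. Each infected intervention woman receives one course; everyone else has a count of zero. The model then has three cells: all controls, intervention with no course, and intervention with one course. The group odds ratio is the odds in intervention women with no course divided by the odds in all controls (0.40/0.60 = 0.667).

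| Assumed enrolment prevalence | Placental malaria if uninfected at enrolment | Group odds ratio under no effect |
|---|---|---|
| 20% | (0.40 − 0.20 × 0.70)/0.80 = 32.5% | 0.481/0.667 = 0.72 |
| 30% | (0.40 − 0.30 × 0.70)/0.70 = 27.1% | 0.373/0.667 = 0.56 |
| 40% | (0.40 − 0.40 × 0.70)/0.60 = 20.0% | 0.250/0.667 = 0.38 |

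The design effect itself is (0.25/0.75)/(0.40/0.60) = 0.50. An ineffective package could therefore show an odds ratio of similar size. The inputs are not in the article, so this shows the mechanism and does not forecast the bias.

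**3. Gain from enrolment infection as a covariate.** Simulated trials with 152 per group, marginal rates held at 40% and 25%, logistic regression with and without a binary enrolment-infection term. With an assumed enrolment prevalence of 30-35% and an odds ratio of 3-6 for placental malaria, power is about 80% without the term and about 82-87% with it. Stronger assumed associations give larger gains: 40% prevalence with 70% placental malaria in infected controls gives about 88%, and with 80% about 94%.

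**4. Events before enrolment, as a conditional calculation only.** Suppose π of the 40 percentage points were fixed before entry and the planned ratio 0.25/0.40 = 0.625 applied only to the rest. The intervention prevalence would be π + 0.625 × (0.40 − π).

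| π (assumed) | Intervention prevalence | Power at 152 per group |
|---|---|---|
| 0 | 25.0% | 80% |
| 4 points | 26.5% | 71% |
| 8 points | 28.0% | 60% |
| 10 points | 28.8% | 54% |
| 15 points | 30.6% | 40% |

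The article gives no value for π and does not say that 0.625 applies to preventable infection alone.

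**The case against.** **The dilution argument.** A reader might infer that the trial is underpowered, at 54% or 40%, because women enter after the period of highest risk. The documents do not support this.

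- The Introduction names the first and second trimesters, and entry at 16 to 24 weeks falls within the second. Screening starts at the first dose, so part of that period is open to the intervention.
- The 40% and 25% are stated for placental malaria as a whole. They read naturally as a net effect that already contains any unpreventable events.
- Adjusting for enrolment infection would not remove dilution. Infections cleared before entry would often be missed at enrolment, and intervention women who are positive at entry should be detected and treated, so their infections are not simply fixed events.

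This objection stands in full.

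**The outcome.** A reader might want past infection dropped. Screening and treatment can turn an active infection into a past one, so an outcome of active infection alone could flatter the intervention group. Counting past infection guards against that. This also stands.

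**The enrolment sample in controls.** The control-group sentence on systematic sampling follows text about symptomatic women. Follow-up rules out additional screening in controls and fixes samples for all women only at days 60 and 80. The wording on scheduled visits and the Abstract favour wider sampling, but a sample from every control at enrolment is not stated outright. If controls were sampled mainly when symptomatic, the covariate would be missing unequally by group. This limits the fix.

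**Analysis plan territory.** The second covariate list is open-ended, and a precision covariate could be left to the analysis plan. Adjustments for study site and for haemoglobin at enrolment are ordinary detail of that kind and form no part of this point. The DHA-PQ term is different, because the protocol names it for the primary analysis.

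**Conclusion.** The point holds for the model. The primary comparison is adjusted for a component of the intervention counted after randomisation, and no baseline infection covariate is named. The first is a fault in what the protocol fixes; its size depends on inputs that the article does not give. The second is a modest missed gain, about 80% to 82-87% power under the assumed prevalence of 30-35% and odds ratio of 3-6, and it depends on an enrolment sample from all controls. Randomisation balances enrolment infection in expectation, so leaving it out costs precision and does not cause bias.

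No sample-size error and no fault in the primary outcome are shown. That some counted events predate randomisation is a reasonable possibility, but the documents do not quantify it.

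**What to change.** 1. Remove the number of DHA-PQ courses from the primary model.
2. Adjust instead for infection status at enrolment, by the same test in both groups (microscopy/PCR). The US-RDT result cannot serve, because only the intervention group has it.
3. First confirm, and state plainly, that every control gives a blood sample at enrolment. If not, the covariate should not be used in the primary model.
4. Keep the primary outcome. Report active and past-only placental infection by group as description only, with a note that treatment can convert active to past infection.
5. State whether 40% to 25% already allows for infection before enrolment.

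The cost is wording in the protocol or analysis plan, plus the handling of a few missing enrolment results. If sampling of controls at enrolment is confirmed, the fix needs no new visits or samples.

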#### Secondary clinical outcomes

Safety profile of DHA-PQ and AL: Adverse events for each study drug will be recorded at all schedules and unscheduled visits.Low birth weight. At delivery each baby will be weighted: The prevalence of low birth weight will be compared between the two groups. Low birth weight will be defined as a birth weight less than 2500 g.Maternal peripheral *P. falciparum* infection (microscopy and PCR) at delivery: Malaria case will be defined as the presence of *P. falciparum* at any stage, regardless of clinical signs. The prevalence of peripheral parasitemia at delivery will be compared between the two groups.Maternal anemia at delivery. The prevalence of maternal anemia at delivery will be compared between the two groups. Anemia will be defined as hemoglobin < 11 g/dL.

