### Follow-up

#### Intervention group

One month after the first ANC visit with the first IPT-SP dose administration, the participant will be invited to the health facility for screened for malaria infection using the US-RDT. From that and at monthly intervals up to the last week of gestation, the pregnant women will be encouraged to visit the ANC clinic where the study nurse will perform a systematic screening using US-RDT and treatment with a full course of DHA-PQ if positive. The first dose will be administered under direct observation during ANC and the subsequent doses on days 2 and 3 will be taken unsupervised at home. The assessment of the treatment observance will be checked by the field worker at the end of the treatment. Before treatment and regardless of the US-RDT result during scheduled and unscheduled visits, the nurse will systematically collect a blood sample for hemoglobin measurement, microscopy, and filter paper for subsequent genotyping.

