The secondary clinical outcomes are pilot endpoints to include incidence rates (mean hemoglobin and birth weight), molecular and parasitological endpoints, safety, determinants of poor coverage of IPTP-SP, vector control effectiveness, and adverse events. Adverse events and serious adverse events will be monitored, managed, and recorded during the study. All study participants who receive at least one dose of the study drug will be included in the safety analysis. They will be recorded and tabulated for each treatment group. All parasitological data will be included in the parasitological analyses. For the evaluation of placental malaria and low birth weight in newborns, logistic regression will be performed while for the evaluation of the occurrence of malaria cases in pregnant women during the follow-up, Poisson regression will be implemented. The stratification or adjustment factors will be among others: the number of doses of IPTg-SP, the season of malaria transmission, and the gravidity. A statistical model will be used for the phone reminder by adjusting the number of calls (0, 1, 2) that the woman in the intervention group received before coming to this ANC. In this model, the number of calls for women in the control group will be 0. For the qualitative study, the acceptability will be assessed through focus group discussion and in-depth interviews. Topics covered by the in-depth interviews will comprise many components such as experience and opinions of the trial intervention groups, perceptions of the acceptability of the trial intervention, and implications for implementation. The interview guide will be used to collect data from pregnant women, health care workers, community health care workers, and traditional healers. The theoretical framework of acceptability developed by Mandeep Sekhon, Martin Cartwright, and Jill J. Francis will be used to assess acceptability. In this study, we will analyze the acceptability through the dimension of the burden, ethical consequences, experience, opportunity cost, intention, and affective attitude. The analysis will focus on the barriers and factors limiting adherence to IPTp-SP uptake.

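### Adverse events are recorded at visits, and only the open intervention group gets reminders and monthly screening visits, so the AE table by group may differ through frequency of contact alone

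*Protocol article*

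**What the plan says.** Under Secondary clinical outcomes, the recording rule for the safety profile of the two antimalarials is "Adverse events for each study drug will be recorded at all schedules and unscheduled visits". Statistical methods limits the safety analysis to women who took at least one dose of study drug and says of adverse events: "They will be recorded and tabulated for each treatment group". No visit denominator, per-visit rate or between-group test for adverse events is stated.

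Planned contact differs by group.

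- **Intervention group.** Under Participant timeline: "A phone call as a reminder will be made 1 week prior to the scheduled date for the second dose of IPTp-SP", and then "If the participant is not reachable, the field worker will visit the household in order to remind the visit date". Under Follow-up, starting one month after the first dose: "From that and at monthly intervals up to the last week of gestation, the pregnant women will be encouraged to visit the ANC clinic".
- **Control group.** Under Participant timeline: "No reminder will be used for the next ANC visit/IPT-SP dose date". Under Follow-up: "No additional screening will be performed in this group".
- **Both groups.** Follow-up (Control group) adds visits at day 60 and day 80 for all women, described for blood sampling. It also says that "field workers will visit the treated participant on day 3 (final day of treatment) in order to assess uptake and compliance to treatment", by questionnaire and a check of empty packs, with referral of women found severely ill. Final study visit adds the delivery contact. The Methods paragraph of the Abstract describes monthly follow-up to delivery for both groups.

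The trial is open. Randomization and blinding and Clinical outcomes describe blinding only for blood films, placental biopsies and PCR.

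**The concern.** If events are recorded at visits, the number of visits is part of the measuring instrument. Here that number is partly set by allocation: phone reminders are one of the three components of the package, and monthly screening brings intervention women to the clinic. With identical true event rates, the group seen more often will tend to have more events on record. The staff who ask about events also know the allocation, which the blinded laboratory readings do not offset.

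Timing adds to this. Both drugs are three-day courses with the second and third days taken unsupervised at home. The one contact near exposure that reaches treated women in both groups is not described as recording adverse events. Mild events may therefore first be asked about at the next clinic visit, perhaps a month later.

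At stake is how the pilot's safety table is read. It feeds the planning of a larger trial, and as specified it cannot separate an effect of drug or package from an effect of being seen more often.

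**Working it through.** **Figures in the plan.** The article gives no adverse-event rate, visit count or safety sample size, so there is no stated figure to reproduce. The sample size for placental malaria (152, then 170 per arm) does not bear on this point.

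**Inputs from the article.** Entry is at 16 to 24 weeks' gestation (Inclusion criteria). Intervention contacts are monthly. Named control contacts are the second-dose date, day 60, day 80 and delivery.

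**Assumptions.** Delivery at 40 weeks; a chance q of recording an event at any one visit, equal in both groups and independent between visits; and the numbers of visits attended. None of these is a figure from the article.

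**Step 1: intervention visits.** 40 − 24 = 16 weeks and 40 − 16 = 24 weeks. At one visit per 4 weeks that is 16/4 = 4 to 24/4 = 6 visits. Take the middle value, 5.

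**Step 2: control visits.** The four named contacts give 4 visits if all are attended and the second-dose date does not coincide with day 60. They give 3 if one is missed or two coincide. If controls also attend monthly, as the Abstract implies, the number is 5.

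**Step 3: share of women with at least one recorded event.** With v visits the share is 1 − (1 − q)^v. At q = 0.10:

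- v = 5: 1 − 0.9^5 = 0.410
- v = 4: 1 − 0.9^4 = 0.344, ratio 0.410/0.344 = 1.19
- v = 3: 1 − 0.9^3 = 0.271, ratio 0.410/0.271 = 1.51

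**Step 4: range over q.** Apparent intervention-to-control ratio with no true difference:

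| q | 5 vs 5 visits | 5 vs 4 | 5 vs 3 |
|---|---|---|---|
| 0.05 | 1.00 | 0.226/0.185 = 1.22 | 0.226/0.143 = 1.59 |
| 0.10 | 1.00 | 1.19 | 1.51 |
| 0.20 | 1.00 | 0.672/0.590 = 1.14 | 0.672/0.488 = 1.38 |

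One fewer control visit thus gives about 1.1 to 1.2, two fewer about 1.4 to 1.6, and equal attendance gives 1.0.

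**Step 5: what the illustration leaves out.** In the treated-only safety set, only contacts after the first dose count, and the article gives no treated proportion or treatment dates from which to work this out. Nor does the illustration model unblinded questioning, which could make q itself differ by group.

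**Step 6: entry to the safety set.** Intervention women enter it after a positive US-RDT at systematic screening. Controls enter it after symptoms followed by a positive HRP-2 RDT. The two sets of treated women are selected differently, and in controls the symptoms of the malaria episode can themselves be counted as adverse events. This can distort the table in either direction, even with equal visits.

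**The case against.** The strongest counter-argument is that unequal visiting is not established. The Abstract has both groups followed monthly, and the control text also refers to scheduled visits. The absence of extra screening in controls does not mean the absence of visits. This stands as a limit on size: with truly equal attendance there is no ascertainment bias. It does not remove the point, because the Follow-up section names monthly clinic visits for the intervention group only, and even on an equal schedule one group is reminded and the other is not. The reminder is described for the second dose, so most of any lasting difference would come from the monthly invitations.

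A second objection is that events after a three-day course depend mainly on the number of courses, that every treated woman gets a day-3 visit, and that nothing forbids recording events there. Statistical methods also says that adverse events are monitored throughout, and a DSMB reviews all safety data. This is fair, and the content of the day-3 form could be detail left to the full protocol. The point rests instead on a stated recording rule combined with stated unequal contact. DSMB review cannot restore events that were never elicited.

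Third, day 60, day 80 and delivery bear no relation to treatment dates, so a comparison confined to them would worsen recall. That stands, and it is why the day-3 visit should carry the tolerability measure.

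A reader might go further than the article allows in three ways:

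- **A threefold ratio**, from 6 intervention visits against 2 control visits. This sets the intervention maximum against a control minimum, although randomisation should make gestational age at entry similar. Low control attendance cannot be read from the 31.5% in the Introduction, which is uptake of at least three IPTp-SP doses, reported alongside high ANC attendance.
- **Concealed DHA-PQ harm.** Extra visits add recorded events in the intervention group. They could mimic harm there or mask an excess on AL, but would not hide harm from DHA-PQ.
- **A false positive test.** The article states only a tabulation of adverse events, with no test.

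**Conclusion.** The concern holds as a possible bias, not a certain one. Recording is tied to visits, the package is built to raise attendance in one open group, and no visit denominator is stated. On assumed attendance of 5 intervention visits and equal true risk, the recorded share would be inflated by a factor of about 1.1 to 1.2 for one missing control visit and 1.4 to 1.6 for two, for q between 0.05 and 0.20. The factor is 1.0 if monthly follow-up is delivered equally. The article does not show which case applies, because the Abstract and the Follow-up section describe control follow-up differently. The treated-only safety set is a separate reason not to read its table as a randomised comparison. The primary outcome is not affected. The change is worth making because it is cheap and the pilot informs a larger trial.

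**What to change.** 1. Reconcile the Abstract with the Follow-up section, so that the planned contacts of each group are stated once and consistently.
2. Add a fixed adverse-event symptom checklist to the day-3 home visit already made to every treated woman in both groups. Use it as the main drug-tolerability measure, with treated courses as the denominator.
3. Keep all adverse events in the safety tables. Show those from contacts common to both groups (day 3, day 60, day 80, delivery), and all SAEs, separately from those found at extra visits. Report the number of visits per woman by group beside them.
4. State that women enter the safety set by different triggers in the two groups (screen-positive versus symptomatic and RDT-positive), so that its table is descriptive and not a randomised comparison.

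The cost is a few questions on an existing form and one further split of the tables; no visit is added. The common-contact table will hold fewer events. Because day 3 is the last treatment day, later-onset events will still depend on subsequent contacts, which is why the remaining events and the visit counts stay in the report.
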